## Abstract

**Background:**

Molluscum contagiosum is a non-severe pediatric viral infection. Because it is highly contagious and current treatments have negative aesthetic and psychological effects, we want to test an alternative treatment in the primary care setting, consisting of two different concentrations of potassium hydroxide solution.

**Methods/design:**

The study design is a double-blind, randomized clinical trial, using three types of topical treatment. The treatment consist of daily applications of potassium hydroxide (KOH) in aqueous solution at 10% and 15% concentration, and a placebo administered in the control group. Four follow-up visits (at 15, 30, 45 and 60 days) are planned to evaluate treatment effectiveness and patient tolerance.

The main outcome measure of the trial will be the healing rate, defined as lesion disappearance in the affected zones after the topic application of the experimental treatment. Secondary measures will be the principal characteristics and evolution of the affected zone (surface area, number of lesions, size and density of lesions), treatment tolerance (hyperpigmentation, itching, burning, pain), recurrence rate and the natural evolution of lesions in the control group.

**Discussion:**

KOH can potentially be an effective and safe treatment for MC in primary care, and can also reduce referrals to dermatologists and hospital pediatric departments. In addition, KOH may be a valid and less expensive alternative to current invasive treatments (surgical excision).

**Trial Registration:**

ClinicalTrials.gov: NCT01348386

## Background

Molluscum contagiosum (MC) is a viral infection of the skin [1] produced by a member of the Poxvirus family, the genus Molluscipoxvirus [2]. The symptoms are the appearance of pearly, usually umbilicated papulae. The lesions are completely asymptomatic and can affect any part of the body, usually affecting the thorax or lower extremities. They usually appear asymmetrically in previously injured zones (wounds or atopic dermatitis). Transmission requires direct contact with the infected host or contaminated fomites. MC frequently affects children using community swimming pools or siblings using the same washing sponges or towels [1-5]. The period of incubation usually oscillates between three and twelve weeks. Clinical diagnosis is based on the detection of the characteristic appearance of lesions. Differential diagnosis includes folliculitis, follicular hyperkeratosis, viral verrucas and insect bites. Lesions cause intense feelings of embarrassment not only to parents but also to children, which sometimes result in school absenteeism and curtailed activities. The natural history of MC is spontaneous regression within six to eighteen months. However, because it is highly contagious, new lesions from the incubating virus may appear later. There is considerable debate as to whether it is necessary to treat the infection. The aesthetic or psychotherapeutic effects of treatment need to be evaluated, as well the ease of transmission of the virus.

Treatment consists of different methods to destroy infected tissue together with the virus. These can be: crude/bloody (curettage, electrocoagulation, clamping, etc.), excessive (oral cimetidine, oral isotretinoin), or topical therapies (salicylic acid, tretinoin or potassium hydroxide) [6]. Since 1999, some studies have been published that satisfactorily tested the use of potassium hydroxide (KOH) [2,7-9] in different concentrations, and imiquimod [10]. However, none of these were tested in a standard pediatric primary care clinic.

Four published studies were found in a clinical bibliographic search. They all concluded that KOH solution is an effective and safe treatment for MC. A notable heterogeneity existed among study methodologies, with different KOH concentrations used for treatment and/or studies lacking a control group.

Only one study was designed as a clinical trial, the others were descriptive designs. All the studies were done in the context of medical specialties other than pediatrics.

The present study will be conducted in a primary care setting, as the point of first contact within the National Health Service (NHS). The aim is to assess the efficacy of topical KOH treatment in 10% and 15% aqueous concentrations, versus a control (placebo) group in a pediatric clinic in a primary care center (PCC) in Lleida (Spain).

A randomized clinical trial (RCT) design has been chosen, with the objective of providing the maximum level of evidence. The treatment will be administered to three groups - one control and two treatment groups. This design will compare both treatment groups to the control group as well as compare the efficacy of the differences doses.

We hypothesize that the daily application of KOH treatment for MC is safe and affective in pediatric patients. Our bibliographic research has identified a paper [7] that estimates a 20% rate of successful resolution with placebo treatment and a 70% success rate with KOH treatment, with a mean treatment period of 54 days. Another study [8] without a control group and twice daily applications of 10% KOH reported 32 successful resolutions of 35 cases during a six month period.

This trial has been approved by the Ethical Committee of Clinical Trials of the IDIAP Jordi Gol (Primary Care Research Institute, Spain)

## Methods/design

### Objectives

#### 1.1 Principal objective

Evaluate the efficacy (disappearance of lesions) of treating MC with daily topical applications of KOH (in concentrations of 10% and 15%).

#### 1.2 Secondary objectives

- To evaluate reductions in the number, size and density of MC lesions in affected areas.

- To evaluate the time lapsed between treatment application and cure (disappearance of the lesions).

- To evaluate tolerance to the treatment.

- To describe the natural evolution of the infection with respect to the number, size and density of lesions in affected areas, based on findings in the control group.

- To compare the differences in efficacy of and tolerance to treatment in the three study groups.

### Trial design

#### 1.1 Summary of trial design

The study will be a double blind clinical trial with random treatment allocation. Patients will be randomized into three parallel treatment arms. Treatment will consist of the application of topical 10% or 15% KOH in an aqueous solution for the two treatment groups, compared to a placebo-treated control group.

A total of five appointments are planned, one baseline and four follow-up visits. Screening will be done during the baseline visit to verify that all patients fulfill the inclusion and exclusion criteria, and have signed a written consent form, in addition to recording sociodemographic variables and a clinical history.

The efficacy of and tolerance to the treatment, as well as the appearance of new lesions, concomitant treatments and adverse affects will be evaluated in the follow-up visits.

During the baseline visit, the patient will be diagnosed and essential information will be recorded (inclusion/exclusion criteria, sociodemographic variables and clinical assessment). All valid/evaluable patients will be assigned a randomization code, up to a maximum of 60 patients who fulfill the inclusion/exclusion criteria. Neither the patient, their parents, nor the pediatrician will know to which group the patient has been assigned. Four follow-up visits are planned, at 15, 30, 45 and 60 days (± 3 days) from baseline. Each visit will include a clinical assessment, where the appearance of new lesions will be recorded. The efficacy of treatment and the tolerance of treated lesions since the last visit will be studied. A photograph of the affected area will be taken. If the patient misses the follow-up visit, compliance will be noted in the completion worksheet (which will be filled out in all remaining cases at 60-day follow-up). The randomization code will be revealed if the attending physician believes this to be appropriate. In this case the patient will be removed from the study, filling out the completion worksheet.

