#### 1.3 Primary and secondary endpoints/outcome measures

Efficacy will be assessed in each of the areas detected in the previous visit. If there are new areas affected, they will be evaluated at the next visit (a description of the new lesion will be recorded in the topographic section of the patients record).

The principle efficacy variable (primary endpoint) will be calculated for each of the affected areas, as an indicator variable: (1. There is a lesion in the area/0. No lesion in the area) at 60 days from baseline. Each patient will be considered cured if they have no lesions in any of the treated areas.

Secondary efficacy variables (secondary endpoints) will be calculated for each location as follows:

- Number of lesions.

- Extent of area affected.

- Mean size of lesions.

○ < 0.5 cm.

○ 0.5 cm. - 1 cm.

○ > 1 cm.

- Efficacy of method: Ordinal scale with five categories.

○ Worsening (net increase in number of lesions or growth of existing ones).

○ No changes *(no modifications to the lesion).*

○ Slight improvement *(disappearance of up to 50% of lesions).*

○ Moderate improvement *(disappearance of more than 50% of lesions).*

○ Cure (*complete disappearance of lesions*) (primary endpoint).

- Digital photograph.

- Lesion density*: Number of lesions/Extent of affected area

*NOTE: If the parents locate new lesions between visits they should NOT treat them until the physician has clinically evaluated their topography*.

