#### 1.7 End of trial assessment

Each study participant can leave the study for two reasons:

1) Loss to follow-up (before the end of follow-up protocol, without successful treatment).

a. Lack of efficacy.

b. Choice of the patient.

c. Adverse effects.

d. Loss to follow-up (missing scheduled visits).

e. Breaking the blind.

f. Other.

2) Completion of follow-up.

g. Attended all scheduled visits

h. Success of treatment

A completion form should be filled out for all patients, whether they have finished the study or not.

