#### 1.8. Statistical methods and sample size

##### 1.8.1. Statistical analysis

The statistical analysis will be carried out on several different samples of the study population. The valid or valuable patient group is defined as those patients that fulfill all the inclusion criteria, none of the exclusion criteria, whose parents have provided consent for their participation and who have been assigned a treatment (randomized code). The safety sample is defined as the group of valid patients who have received treatment in the study at least once, whether or not its effectiveness has been assessed (who came to at least one follow-up visit). The intention to treat (ITT) sample is defined as the group of valid patients who have received treatment at least once and who have been assessed for its effectiveness at least once. The per protocol (PP) sample is defined as the group of patients that make up the ITT sample, have been assessed for efficacy and have not violated the protocol in any of the following ways:

- Violation of blinding.

- Greater than 10% missed treatments.

- Loss to follow-up by missing a scheduled visit.

The unit of analysis is the patient. Nevertheless, each patient can present multiple affected areas. An area is considered to be a set of lesions whose perimeter does not coincide with another affected area, with a single area being possible. No more than 15 affected areas per patient are expected.

A descriptive analysis of all the variables collected will be done, expressing quantitative variables as means, medians, minimums, maximums and standard deviations (SD), and categorical variables as frequencies and percentages.

The homogeneity of the study groups with respect to the following baseline parameters will be compared:

Demographic variables

Initial topography

Clinical history of associated diseases

History of treatments received (> 1 month)

To determine the existence of an association between a group and secondary efficacy variables at each period of follow-up, the single-factor ANOVA test will be used for quantitative variables (extent, number of lesions, etc.) and the chi-squared test will be used for categorical variables (cure).

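### Read together, the missed-visit rules treat one missed interim visit as loss to follow-up, so an uncured child's obtainable day-60 primary outcome can be lost

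*Protocol article*

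**What the plan says.** All references are to the protocol article.

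- **Endpoint.** Section 1.3 reads the primary endpoint once, "at 60 days from baseline". Section 1.8.2 sizes the trial on complete elimination at that same final visit.
- **Schedule.** Section 1.1: "Four follow-up visits are planned, at 15, 30, 45 and 60 days (± 3 days) from baseline".
- **What happens at a missed visit.** Section 1.1: "If the patient misses the follow-up visit, compliance will be noted in the completion worksheet", followed in brackets by "which will be filled out in all remaining cases at 60-day follow-up".
- **Leaving the study.** Section 1.7 lists "Loss to follow-up (missing scheduled visits" among the reasons for leaving. That category applies "before the end of follow-up protocol, without successful treatment". The two routes to completion are "Attended all scheduled visits" or success of treatment.
- **Analysis sets.** Section 1.8.1 lists "Loss to follow-up by missing a scheduled visit" as a protocol violation that excludes a child from the per-protocol sample. The ITT sample keeps any valid child treated at least once and assessed for efficacy at least once.

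**The concern.** None of these rules distinguishes a missed day-15, day-30 or day-45 visit from a missed day-60 visit, yet only day 60 supplies the primary outcome. A site following the text could complete the closing form for an uncured child who missed day 30, code the child as lost, and not hold the day-60 visit. That child's primary outcome would then be missing although it could have been collected.

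The harm would not be confined to the per-protocol sample. A child assessed once stays in the ITT sample, but with no day-60 observation. A statistical analysis plan can say how to handle that gap but cannot recover the observation.

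The loss would also depend on outcome. A child recorded as cured leaves as a treatment success and counts as a completer. Only children not yet cured are exposed to this route of loss. Because the plan expects 20% cure on placebo and 70% on KOH, the arms would be exposed unequally.

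**Working it through.** **1. Do the rules add up to close-out?**

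- In section 1.1 the form used at a missed visit is the completion worksheet. The remaining cases have theirs filled out at day 60, so the child who missed a visit is set apart from them. The same worksheet closes out a child whose code is broken.
- In section 1.7 an uncured child who misses day 30 but attends day 60 has not attended every visit and is not a treatment success. Neither completion route fits, which leaves loss to follow-up as the nearest category.
- Section 1.8.1 uses the singular and calls one missed visit loss to follow-up.
- Nowhere does the article say that a child who missed an interim visit is still assessed at day 60.

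The per-protocol exclusion is therefore explicit, and close-out is inferred from the three sections together.

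**2. The plan's own sample size.** Inputs from section 1.8.2: cure 20% versus 70%, power 80%, significance level 5% (taken as two-sided), loss 20%. With the pooled normal formula without continuity correction, the mean proportion is 0.45:

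n = [1.96 × √(2 × 0.45 × 0.55) + 0.842 × √(0.2 × 0.8 + 0.7 × 0.3)]² / 0.5² = (1.379 + 0.512)² / 0.25 ≈ 14.3, so 15 per group.

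15 / 0.8 = 18.75, so 19 per group. The stated 20 is reproduced to within one patient.

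**3. Size of the avoidable loss.** The article gives no per-visit miss rate. Let q be an assumed probability of missing each visit, independent across visits, and take every child as still uncured at all three interim visits.

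- Misses at least one interim visit: 1 − (1 − q)³
- Misses an interim visit but would attend day 60 (the avoidable loss): [1 − (1 − q)³] × (1 − q)
- Misses any of the four visits: 1 − (1 − q)⁴, which equals the avoidable loss plus q

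| q (assumed) | Misses ≥ 1 interim | Avoidable loss | Any of four | Day 60 only |
|---|---|---|---|---|
| 2% | 5.9% | 5.8% | 7.8% | 2% |
| 5% | 14.3% | 13.5% | 18.5% | 5% |
| 10% | 27.1% | 24.4% | 34.4% | 10% |

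The avoidable share of 20 children per group is about 2.7 at q = 5% (20 × 0.135) and 4.9 at q = 10% (20 × 0.244). Loss under the any-visit rule reaches the planned 20% at q = 1 − 0.8^(1/4) = 5.4%.

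**4. Power for 20% versus 70%.** With n observed per group, power = Φ{[0.5√n − 1.379] / √0.37}.

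| q (assumed) | n left of 20, any-visit rule | Power | n left of 20, day 60 only | Power |
|---|---|---|---|---|
| 2% | 18.4 | 0.90 | 19.6 | 0.92 |
| 5% | 16.3 | 0.85 | 19.0 | 0.91 |
| 10% | 13.1 | 0.76 | 18.0 | 0.89 |

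These power figures treat the lost children as a random subset. They show lost precision only, not the bias from loss that depends on cure.

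**The case against.** The strongest reply is that no sentence removes the child. Section 1.1 states removal outright for code-breaking and does not do so for a missed visit. Section 1.7 lists reasons why a participant may leave, uses the plural for missed visits, and does not bar a later day-60 visit. The source is also a condensed article, and rescheduling procedures may sit in the full protocol. This stands as far as it goes: a reader might infer that the protocol orders exit after a single missed interim visit, and it does not say so. But three stated rules point the same way and none points the other way.

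Other points on that side hold and limit the concern:

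- A missed interim visit is not irrelevant to treatment. Section 1.3 has parents leave new lesions untreated until the physician has evaluated them, and it assesses efficacy in the areas found at the previous visit. Section 1.2.3 routes reports of stopped treatment through the next visit. Excluding irregular attenders from a strict per-protocol set is therefore defensible.
- A reader might suppose that a visit outside the ± 3 days counts as missed. The article does not say that.
- A reader might picture a child already recorded as clear being lost for skipping a visit. Section 1.7 counts that child as a treatment success.
- It is tempting to say that at q = 5% this rule alone nearly exhausts the 20% allowance, because 18.5% miss some visit. That figure includes 5% who miss day 60 and are lost under any rule.
- The miss rates are assumed. Clustering of misses within families would lower the share who miss at least one visit, and at q = 5% power stays above 80%.

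**Conclusion.** The concern holds as a joint reading of sections 1.1, 1.7 and 1.8.1. They treat a missed scheduled visit as loss to follow-up without separating the interim visits from day 60. Followed literally, they can forfeit an obtainable primary outcome in ITT as well as per-protocol, and only for children not yet cured.

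The avoidable share is about 13.5% at an assumed 5% miss rate per visit and 24.4% at 10%, against a 20% allowance meant to cover all losses. Both figures rest on independent misses and on every child remaining uncured through day 45. They are therefore upper values wherever cure comes earlier, and should be closest to the truth on placebo. Power falls below 80% only at the higher assumed rate.

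The documents do not support the stronger conclusion that the plan expressly discards these outcomes, nor that the strict per-protocol criterion is itself an error. The point is worth acting on because data collection at the site is at stake and the correction is cheap.

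**What to change.** - **Sections 1.1 and 1.7:** state that a missed interim visit is recorded as a missed visit, that the child stays in the study, and that the day-60 efficacy assessment is still held and used in the ITT analysis. Leave use of the completion worksheet at code-breaking and the other exits as it is.
- **Section 1.7:** let an uncured child who missed an interim visit but attended day 60 be classed as having completed follow-up.
- **Section 1.8.1:** the per-protocol sample may stay strict, but name the criterion a missed scheduled visit, so that one missed interim visit is not equated with loss to follow-up.

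The cost is wording only, since the day-60 visit is already planned. The small downside is that some retained children will have gaps in the interim secondary data and in the list of affected areas. If retention was always intended, the same edit prevents sites from reading the text otherwise.

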#### 1.2 Description of the measures taken to minimize/avoid bias

##### 1.2.1 Randomization and codebreaking

Randomization will be centralized at the Pharmacy Department of the hospital of reference, the Arnau de Vilanova University Hospital (HUAV).

Patients will be randomly allocated to one of the study groups. Randomization will increase the probability of distributing patients to the three groups homogenously.

##### 1.2.2 Blinding

The vials of solution to be studied will be prepared as follow:

- KOH 10%: 10 grams of KOH dissolved in purified water, 100 ml

- KOH 15%: 15 grams of KOH dissolved in purified water, 100 ml

- Placebo: 100 milliliters of saline solution

The vials will be indistinguishable, regardless of content, and will be stored at room temperature. A mask and gloves are required for preparing the solutions.

##### 1.2.3 Other measures taken to minimize/avoid bias

HOMOGENEOUS APPLICATION: Each patient will receive a bottle of the solution assigned (identical bottles), depending on their randomization code. The parents/guardians of the patient will be shown how to apply the solution to the lesions, and written instructions will be provided, as follows: the treatment should be applied once per day with a cotton swab soaked in the solution, unless the lesion shows signs of INFLAMMATION OR IRRITATION, at which point the TREATMENT SHOULD BE STOPPED (parents should write down the date in order to inform the physician at the next follow-up visit).

#### 1.3 Primary and secondary endpoints/outcome measures

Efficacy will be assessed in each of the areas detected in the previous visit. If there are new areas affected, they will be evaluated at the next visit (a description of the new lesion will be recorded in the topographic section of the patients record).

The principle efficacy variable (primary endpoint) will be calculated for each of the affected areas, as an indicator variable: (1. There is a lesion in the area/0. No lesion in the area) at 60 days from baseline. Each patient will be considered cured if they have no lesions in any of the treated areas.

Secondary efficacy variables (secondary endpoints) will be calculated for each location as follows:

- Number of lesions.

- Extent of area affected.

- Mean size of lesions.

○ < 0.5 cm.

○ 0.5 cm. - 1 cm.

○ > 1 cm.

- Efficacy of method: Ordinal scale with five categories.

○ Worsening (net increase in number of lesions or growth of existing ones).

○ No changes *(no modifications to the lesion).*

○ Slight improvement *(disappearance of up to 50% of lesions).*

○ Moderate improvement *(disappearance of more than 50% of lesions).*

○ Cure (*complete disappearance of lesions*) (primary endpoint).

- Digital photograph.

- Lesion density*: Number of lesions/Extent of affected area

*NOTE: If the parents locate new lesions between visits they should NOT treat them until the physician has clinically evaluated their topography*.

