In the case that the ANOVA cannot be used because a quantitative parameter does not fulfill the application criteria (non-normality/heteroscedasticity) the data will be transformed (logarithmic) from the original parameter, or a non-parametric analog test (Kruskal-Wallis) will be used. In all 2 × 2 comparisons (Group I, II vs. Placebo), the significance level will be adjusted for multiple comparisons.

The evolution of the quantitative efficacy parameters will also be assessed, by group, for the different time periods, using a repeated measures analysis.

The relationship between the baseline variables and the efficacy variables will be assessed at the end of the study, and in the case that an association is found, a multivariate analysis will be carried out to assess possible confounding factors of the group effect on adjusted efficacy: a multiple regression analysis will be used in the case of quantitative efficacy variables and a multinomial regression will be used in the case of qualitative variables.

The time from treatment to cure will be calculated as the difference between the date of first treatment and the disappearance of lesions or the end of the study (treatment initiation). Survival tables and the Kaplan-Meier statistic will be calculated to compare cure times between the different treatment groups. In the case that associations are found between efficacy variables and baseline conditions, a Cox proportional risk model will be adjusted.

Data analysis will be by ITT, by protocol and by safety sample.

In all cases a p-value below 0.05 will be considered significant.

Data will be analyzed using the statistical package "R": http://www.r-project.org.

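### Lesion density and mean size have no value once a child is clear, so at day 60 these two secondary comparisons may rest mainly on uncured children

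*Protocol article*

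**What the plan says.** Section 1.3 lists the secondary efficacy variables, calculated for each location. Three matter here:

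- "Extent of area affected", recorded as an outcome in its own right.
- "Mean size of lesions", in three classes: below 0.5 cm, 0.5 to 1 cm, and above 1 cm.
- Density, given as "Number of lesions/Extent of affected area". Nothing says whether the extent is that of the current visit, an earlier visit or baseline.

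The same list contains "Efficacy of method: Ordinal scale with five categories", whose top level is cure. Section 1.8.1 describes an area by its lesions: "An area is considered to be a set of lesions whose perimeter does not coincide with another affected area".

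Section 1.8.1 sets out the tests. Their stated purpose is "To determine the existence of an association between a group and secondary efficacy variables at each period of follow-up". Quantitative outcomes such as extent and lesion count are compared by one-way ANOVA, and categorical ones by chi-squared. If the ANOVA conditions fail, "the data will be transformed (logarithmic) from the original parameter". Kruskal-Wallis is the alternative offered in the same sentence. No rule chooses between the two, and no offset is given for the logarithm. Reducing the number, size and density of lesions is the first of the listed secondary objectives.

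**The concern.** The trial hopes to produce cleared skin, and two of its secondary variables have no stated value in that state. If extent is taken at the current visit, a cleared area has zero lesions over zero extent. Its mean size falls in none of the three classes. Software would normally treat both as missing.

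If that happens, the children who leave the density and size comparisons are those who responded fully, and an effective KOH arm loses more of them than placebo does. What remains is a subset chosen by an outcome after randomisation. The comparison of that subset no longer has the protection of random allocation. It answers how dense or large the lesions are among treatment failures, which is not the stated objective. A real benefit could go unseen on these two measures.

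**Working it through.** **Inputs.** From section 1.8.2: cure 20% on control and 70% in one KOH arm, power 80%, significance level 5%, loss 20%, and 20 children per group.

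**The plan's own figure.** For a two-sided test with pooled variance and no continuity correction, the mean proportion is (0.2 + 0.7)/2 = 0.45, and

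n = [1.96 × √(2 × 0.45 × 0.55) + 0.842 × √(0.2 × 0.8 + 0.7 × 0.3)]² / 0.5² ≈ 14.3, rounded up to 15.

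Allowing for loss, 15/0.8 = 18.75, or 19 per arm. The stated 20 is consistent with this. The sample size does not depend on the present point, but its cure rates do feed the next step.

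**Children with a defined density or size at day 60, if cleared children have none.** Evaluable per arm: 20 × 0.8 = 16.

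| Arm | Cured | Value defined |
|---|---|---|
| Placebo, 20% cure | 16 × 0.2 = 3.2 | 16 × 0.8 = 12.8 |
| KOH arm at 70% cure | 16 × 0.7 = 11.2 | 16 × 0.3 = 4.8 |

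Without loss, the same calculation on 20 per arm gives 16 against 6. The cure rate of the other KOH arm is not stated. If it lay anywhere from 20% to 70%, between 12.8 and 4.8 of its 16 children would have a value. With 16 children and a 30% chance of not being cured, the binomial probability that three or fewer remain in a KOH arm at 70% is 0.246.

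**What dropping would cost.** A simulation of lesion counts (3,000 runs per scenario, 16 per arm) shows the order of the loss. It is an illustration by analogy, since it models counts and not density or size. Its assumptions are not in the documents: 70% cure in both KOH arms, and residual counts in uncured children of one plus a negative binomial variable with mean 12 and dispersion 1.5.

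| Scenario | Power, cured kept at 0 | Power, cured dropped |
|---|---|---|
| KOH acts only through cure | 81% (Kruskal-Wallis), 79% (ANOVA on log(x+1)) | 4% |
| KOH also halves the excess over one lesion in uncured children | 94% | 22% to 25% |

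In about 5% of runs some arm had fewer than two children left after dropping. Those runs are left out of the right-hand column.

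**Which variables are affected.** After clearance:

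- Density: 0/0 at the current visit.
- Mean size: no class.
- Number and extent: plain zeros, accepted by ANOVA and by Kruskal-Wallis. Only the plain logarithm fails.
- Ordinal efficacy scale: has a cure level.
- Time to cure: the event itself.
- Primary endpoint: coded 0 for an area without lesions.

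**The case against.** The strongest reply is that the text does not establish 0/0. Section 1.3 has efficacy assessed in the areas found at the previous visit and codes an area without lesions as 0, so an area can outlive its lesions as a location. Zero lesions over an earlier extent would then give a density of 0. This is a possible reading, but nothing in the article selects it: density carries no time point and extent is itself a follow-up outcome. It also does nothing for mean size, which lacks a class on any reading.

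It is also fair to say that no sentence excludes cured children, and that a coding rule or log offset could sit in an analysis plan that is not shown. Dropping is therefore the default result of an undefined value and not a stated rule. The endpoint definitions, however, are fixed in this article, and they leave the gap. Variables are recorded per location, so a child with one clear and one active area may still have a value. Only fully cleared children are lost.

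Four stronger readings are tempting and are not supported:

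- *All secondary tests drop the cured children.* Number, extent, the ordinal scale and time to cure retain them.
- *The plan commits to a logarithm that fails.* The logarithm is one of two fallbacks. Kruskal-Wallis is offered in the same sentence, and first-line ANOVA accepts zeros.
- *The secondary results could contradict the primary one.* The illustration shows lost power. It does not show a reversal against KOH.
- *Density is misleading because it can rise as a child improves.* In a hypothetical case, 10 lesions in 20 cm² (0.5) becoming 5 in 5 cm² (1.0) doubles it. Density measures concentration, and number and extent are reported beside it, so the improvement would still be seen.

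**Conclusion.** The point holds for lesion density and mean size. Under the definitions in section 1.3, with extent taken at the current visit, a fully cleared child has neither. Unless a value is assigned, the day-60 comparison would involve about 13 of 16 placebo children and about 5 of 16 in a KOH arm that meets the planned rate. That is a comparison selected by outcome, on a stated secondary objective, and it can hide benefit.

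The figures assume the plan's cure rates, 20% loss unrelated to cure, and that a cured child has no active area left. Section 1.8.2 gives 70% for only one KOH arm, so applying it to both is an assumption. The counts are for day 60 only. The power figures rest on assumed residual counts and indicate direction and order of size only.

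The primary endpoint and the other secondary variables are unaffected, except that a plain logarithm of number or extent, if chosen, is undefined for the same cleared children.

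**What to change.** In section 1.3, state that density is 0 for a cleared area, and add a no-lesion class as the lowest level of mean size. In section 1.8.1, state that variables with zeros (number, extent, density) are analysed by the Kruskal-Wallis test already offered when the ANOVA conditions fail, with cured children kept at zero, and remove the plain logarithm.

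Using the baseline extent as a fixed denominator looks like an alternative but is weaker. Areas that first appear after baseline, which section 1.3 foresees, would have no baseline extent, and density would become largely a rescaled lesion count.

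The cost is a few lines of wording and a line of derivation code. The downside is that a density of 0 is a convention, and that density and size would then partly reflect cure. Reporting both among uncured children as well, as description without a between-arm test, would keep that information visible.
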